#### Secondary outcomes

Secondary outcomes are treatment efficacy and technical results of the stabilization splints. In the present trial, treatment efficacy is defined as the extent of abrasion of the opposing dentition in the bruxism cohort since the reduction of teeth abrasion is the therapeutic rationale for splint incorporation in bruxers. Teeth abrasion is measured as volume loss of the opposing dentition by superimposing intraoral scans obtained at digital impression taking and 3 months control appointments. Treatment efficacy in the TMD cohort is additionally investigated by quantification of pain reduction as the lead symptom of pain-related TMD. For this, the GCPS is evaluated on the day of incorporation and control appointments. The differences in the values obtained for chronic pain intensity (point score between 0 and 100), disability days (between 0 and 30), and interference score (point score 0–100) at control appointments and incorporation days are then calculated for every participant and splint type. Further, the number of painful points on examination according to the DC/TMD is compared at control appointments versus the incorporation date (range 0 to 48). Jaw mobility is investigated by measuring maximum jaw opening, laterotrusion, and protrusion in millimeters at incorporation and control appointments.

In addition, the technical results of 3D printed and milled stabilization splints are compared. Fit at incorporation is evaluated by calculating the amount of adjustment necessary in µm^3^ by overlaying scans before and after adjustment of the splint. Wear of the occlusal splints is assessed by calculating volume loss in µm^3^ by overlaying scans of the splints obtained at incorporation and the 3 months control. The integrity of the occlusal splints (no fracture of the occlusal splint) is assessed at control appointments, and the rate of fractures occurring is calculated in percent for each type of splint.

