Inclusion criteria: The patients seek medical treatment because of pain located in the TMJ and/or jaw muscles. Patients are included in the clinical trial if a myalgia or myofascial pain of the jaw muscles and/or arthralgia of the temporomandibular joint(s) according to the DC/TMD are diagnosed and if the Graded Chronic Pain Scale version 2.0 (GCPS) adopts a maximum of grade II.Exclusion criteria: Patients with GCPS grade III or IV are excluded from the clinical trial. Furthermore, patients with orofacial pain of dental, traumatic, or systemic origin requiring medical treatment other than or prior to splint therapy are excluded. In addition, patients are excluded if they received treatment for TMD that could potentially affect the outcome of the splint treatment, such as insertion of a splint in the month prior to the trial, or injections of botulinum toxin into the jaw muscles in the 6 months prior to the trial. TMJ(s) should not show any pain on traction.

The patients of the TMD cohort are diagnosed and treated by dentists who have more than 7 years of clinical experience in the field of prosthetic dentistry and TMD and who have attended structured postgraduate programs in TMD. The dentists were trained and calibrated in the clinical application of the DC/TMD by gold standard examiners in a course of the INfORM Training and Reliability center, University of Leipzig, Germany. The bruxism cohort is treated by a doctorate candidate in dentistry who is supervised by a dentist from the TMD cohort.

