Incorporation of the 1^st^ splint (T1): scan of the splint as delivered from the laboratory with the intraoral scanner and—if necessary—also after adjustment, completion of the Oral Health Impact Profile (OHIP-G14, German version from 2005) by all participants of both cohorts, completion of the GCPS by participants of the TMD cohort, examination of the TMD patients according to the DC/TMD standardControl 2 weeks after incorporation of 1^st^ splint (T2): if necessary, adjustment and scan of the splint, completion of the OHIP-G14 and GCPS and examination of TMD patients as described above, rating of wear comfort and retention of the stabilization splints on a VAS scale of 1–10 by participants of both cohortsControl 3 months (11–13 weeks) after incorporation of the 1^st^ splint (T3): scan of the splint and opposing dentition with the intraoral scanner, completion of the OHIP-G14 and GCPS, examination of TMD patients and rating of wear comfort and retention as described for T2, scan of the 2^nd^ splint as delivered from the laboratory and—if necessary—also after adjustment, incorporation of the 2^nd^ splint.Control 2 weeks after incorporation of 2^nd^ splint (T4): see T2Control 3 months (11–13 weeks) after incorporation of the 2^nd^ splint (T5): see T3. Additionally, the participant is asked to name his or her favorite splint (1^st^ or 2^nd^)

A wash-out period between the two splints was not included, as this may lead to aggravation of symptoms and therefore bears the risk that patients may switch to alternative treatment options such as commercially available splints to alleviate symptoms during the wash-out period, rendering trial conditions less controlled.

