## Statistical methods

### Statistical methods for primary and secondary outcomes {20a}

Absolute and relative frequencies are calculated for binary or categorical variables. For continuous data, the median, mean and standard deviation are specified. In addition, 95% confidence intervals are calculated. The calculations are performed per group (milled and 3D printed) and per cohort (bruxism and TMD). Cross-over effects are examined in all analyses. For the primary outcome parameter OHIP-G14, the group differences are estimated and tested using a linear regression model with corresponding two-sided 95% confidence intervals. The model will include the difference in OHIP-G14 values (milled vs. 3D printed) as a dependent variable and the sequence of the splints and the cohort (bruxism and TMD) as independent variables.

The one-sided test for non-inferiority of 3D printed versus milled splints at the 2.5% significance level is based on the two-sided 95% confidence interval of the linear regression model. The null hypothesis is rejected if the lower limit of the confidence interval for the difference (conventionally milled vs. 3D printed) is above − 5. The same applies to secondary outcomes, namely volume loss of the splint/opposing dentition, pain reduction, jaw mobility, and splint fracture rates.

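### GCPS disability days need a look-back of at least 30 days, so the per-splint change at the 2-week visits captures only 14 days on the current splint and dilutes the splint contrast

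*Protocol article*

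**What the plan says.** The Protocol article, under Secondary outcomes, lists "disability days (between 0 and 30" as one of three GCPS values used to quantify pain reduction in the TMD cohort. On timing, "the GCPS is evaluated on the day of incorporation and control appointments". The differences "at control appointments and incorporation days are then calculated for every participant and splint type".

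The schedule in Intervention description {11a} includes the GCPS at T2, 2 weeks after the first splint: "completion of the OHIP-G14 and GCPS and examination of TMD patients as described above". T4, 2 weeks after the second splint, refers back to T2. The later control comes at "3 months (11–13 weeks) after incorporation of the 1^st^ splint (T3"), and T5 mirrors it for the second splint. The second splint is inserted at T3, and "A wash-out period between the two splints was not included".

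Statistical methods {20a} sets out the non-inferiority rule for OHIP-G14 and then extends it: "The same applies to secondary outcomes, namely volume loss of the splint/opposing dentition, pain reduction, jaw mobility, and splint fracture rates".

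The article does not state the look-back of the disability-day item in words. It does not shorten the recall at T2 and T4, and it does not restrict the item to the 3-month visits.

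**The concern.** A count of days cannot exceed the number of days it covers, so an item that can reach 30 looks back at least 30 days. Two weeks after insertion, that window extends past the start of the current splint. At T2 it reaches into the time before any trial splint, and at T4 into the time on the other splint.

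The plan nevertheless derives a per-splint change at those visits. Only part of the window can respond to the current splint, so a real difference between milled and printed splints shows up smaller than it is. In a superiority comparison that would be conservative. In a non-inferiority comparison it works the other way, because a contrast pulled towards zero makes it easier to conclude that printed splints are not inferior.

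**Working it through.** **Inputs from the Protocol article**
- Range 0 to 30 (Secondary outcomes), so the window is at least 30 days. I take 30; a longer one would make the overlap larger.
- T2 and T4 fall 14 days after incorporation. T3 and T5 fall at 11–13 weeks, which is 77–91 days (Intervention description {11a}).
- There is no wash-out and the second splint is inserted at T3, so the T3 score is the baseline of the second splint.
- The planned score is the change from incorporation (Secondary outcomes).

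**Assumptions.** The daily rate of disability days is constant within each condition: p before any trial splint, a on splint A, b on splint B. There is no other carry-over. The two sequences get equal weight. The true difference over a full window is D = 30(a − b).

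**Step 1: share of the window before the current splint**
- Day 14: 30 − 14 = 16 days; 16/30 = 53%. On the current splint: 14/30 = 47%.
- Days 77–91: 0 days.

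**Step 2: planned change at 2 weeks**
- T2 on A: (16p + 14a) − 30p = 14(a − p).
- T4 on B after A: (16a + 14b) − 30a = 14(b − a).

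The 16 earlier days appear in both scores and cancel, leaving 14 days on the current splint set against the previous state.

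**Step 3: contrast of changes, A minus B**
- A first: 14(a − p) − 14(b − a) = 14(2a − b − p).
- B first: 14(a − b) − 14(b − p) = 14(a − 2b + p).
- Average: 14 × 3(a − b)/2 = 21(a − b) = 0.70 D.

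**Step 4: the same contrast at 3 months.** Replace 14 by 30: 45(a − b) = 1.50 D. The ratio of 2 weeks to 3 months is 0.70/1.50 = 14/30 = 47%. The 3-month figure exceeds D because the second splint's baseline is taken on the first splint.

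**Step 5: comparing the scores themselves instead of changes**
- T3 against T5: 30(a − b) = 1.00 D.
- T2 against T4: A first gives 16p − 2a − 14b and B first gives 14a + 2b − 16p. The average is 6(a − b) = 0.20 D. The plan does not propose this comparison.

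**Illustration with assumed rates** of 0.3 (no splint), 0.1 (milled) and 0.2 (printed): D = 30 × 0.1 = 3.0 days. The change-score contrast is 2.1 days at 2 weeks and 4.5 days at 3 months.

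**Sensitivity to the actual visit day v.** Share before the splint = (30 − v)/30; change-score contrast = 1.5 × v/30 × D.

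| Day | Before current splint | Contrast |
|---|---|---|
| 11 | 63% | 0.55 D |
| 13 | 57% | 0.65 D |
| 14 | 53% | 0.70 D |
| 15 | 50% | 0.75 D |
| 16 | 47% | 0.80 D |
| 21 | 30% | 1.05 D |

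By day 21 the baseline inflation offsets the dilution. The contrast is still 21/30 = 70% of the 3-month one.

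**The case against.** The strongest reply is that the planned score is a change, not a raw count. The 16 shared days cancel, so other-splint days do not sit in the change as unmatched noise. This is correct, and it rules out a stronger reading that a reader might infer: that 80% of the splint difference is lost. That figure belongs to a direct T2-against-T4 comparison of scores, which the plan does not make. What remains is a reduction in scale, to 0.70 D.

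Other parts of the reply also stand:
- The 47% ratio uses a 3-month contrast that is itself 1.5 times the true difference. Measured against the true difference, the 2-week loss is 30%.
- Only the T4 score mixes both splints. At T2 the earlier days precede any trial splint. Even calling them splint-free is approximate, because eligibility rules out only "insertion of a splint in the month prior to the trial".
- The majority of 16 in 30 is narrow. It becomes half on day 15 and a minority from day 16, and the article gives no visit window for the 2-week control.
- Statistical methods {20a} names pain reduction but gives no visit and does not name disability days. A non-inferiority test of this item at 2 weeks is therefore possible under the text, not stated by it.
- Eligibility admits GCPS grades only up to II, so counts may be low and there may be little difference to dilute.

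The reply does not remove the attenuation. Adjusting for sequence does not help, because the overlap occurs in both sequences. Examining cross-over effects targets carry-over, whereas this arises from the recall window even with no carry-over. The change per splint at the control visits is stated in the article, so this is not a detail left to another document.

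**Conclusion.** The point holds in a limited form. With a 30-day window, a visit on day 14 and steady daily rates, the planned 2-week change in disability days reflects 14 days on the current splint. Its milled-versus-printed contrast is 0.70 of the true difference (30% too small) and 47% of the 3-month contrast. If the non-inferiority rule is applied at that visit, the dilution favours a finding of non-inferiority.

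The 30-day window is inferred from the printed range; the rates are assumptions. The scope is one secondary item, in the TMD cohort, at T2 and T4. The primary OHIP-G14 outcome is not touched by this argument, and at 77–91 days a 30-day window lies wholly on one splint.

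A reader might extend the point to GCPS pain intensity and interference. The article gives no look-back for those 0–100 scores, so it does not support that step. Nor is the 3-month change score free of trouble: its window is clean, but its contrast is inflated by the baseline taken on the first splint.

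**What to change.** Add one sentence to the outcome and analysis sections: the splint comparison of GCPS disability days, and any non-inferiority statement on it, rests on the T3 and T5 values compared directly; T2 and T4 values are reported descriptively. Comparing the values themselves, not the changes from incorporation, gives 1.00 D under the model above and avoids the inflated baseline.

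State the look-back of the item as printed on the form. Apply the same restriction to the other GCPS scores only if the form gives them a look-back longer than 2 weeks.

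No new data or visits are needed. The cost is that the 2-week splint comparison of this item is given up.

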## Interventions

### Explanation for the choice of comparators {6b}

Milled splints are used as comparators as subtractive manufacturing represents the standard CAM fabrication technique for splints. Another option would have been to use splints fabricated conventionally by alginate/silicone impression, cast fabrication, wax-up, and molding from powder-liquid mixtures of PMMA as comparators. It was decided to use milled splints as a comparator since the digital procedure will replace conventional processes due to better time-efficiency and patient comfort [18–20]. In addition, the comparison of two splints fabricated using different CAM processes enables the comparison of splints based on the same digital design and therefore allows differences in splint design/shape to be ruled out as the cause of possible differences in clinical outcome. In contrast, conventionally fabricated and digitally fabricated splints would differ in splint design/shape rendering direct comparison of the effects of the fabrication mode on clinical outcome infeasible.

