## Assignment of interventions: blinding

### Who will be blinded {17a}

Participants are blinded since they are not told how the splint was fabricated. Further, the statistician analyses the data generated during the trial blinded. Treating dentists cannot be blinded since trained personnel can differentiate between a 3D printed and milled splint.

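### The fit outcome is adjustment volume alone, set by an unblinded dentist, and a loose splint left unadjusted scores zero, so it should not carry a conclusion on fit by itself

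*Protocol article*

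**What the plan says.** Under Outcomes {12}, Secondary outcomes, the protocol article gives fit one definition: "Fit at incorporation is evaluated by calculating the amount of adjustment necessary", expressed as a volume and obtained by superimposing the scans made before and after the adjustment.

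Intervention description {11a} says when those scans are made. At delivery there is a "scan of the splint as delivered from the laboratory with the intraoral scanner and—if necessary—also after adjustment". The second scan therefore exists only when someone judges adjustment to be needed. The same holds for the second splint at T3.

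Who will be blinded {17a} states: "Treating dentists cannot be blinded since trained personnel can differentiate between a 3D printed and milled splint". Concealment mechanism {16b} says the same of the personnel who treat. For participants, {17a} states: "Participants are blinded since they are not told how the splint was fabricated".

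Two further places matter. Under Primary outcomes, participants rate from 1 to 10 how stably each splint rested, at 2 weeks and 3 months, and the ratings are compared by manufacturing method; {11a} calls this item retention. Explanation for the choice of comparators {6b} says that using two computer-aided processes "enables the comparison of splints based on the same digital design".

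**The concern.** A measure of fit should worsen as a splint departs from the teeth in either direction. Adjustment volume responds to only one kind of departure, the kind that leads the dentist to adjust. Looseness that prompts no adjustment adds nothing, so it is scored like a perfect fit.

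The amount of adjustment is also a judgement. The article states no criterion for when adjustment is necessary, and the person judging knows the manufacturing method. The blinded statistician cannot remove a difference in judgement that is already in the scans.

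Fit is not incidental. Background and rationale {6a} lists it within the key parameters of successful splint therapy, and the abstract says the trial will support a decision for or against a manufacturing process. How accurately the splint is made is a direct product of that process, so a fit score that can reward looseness could mislead on this component.

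**Working it through.** There is no stated figure to reproduce, because the article gives no adjustment volumes and no looseness rates. The check is therefore a reading of the definition, followed by two illustrations on assumed values.

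**Step 1. What an unadjusted splint scores.** Fit is the volume difference between the scans before and after adjustment (Secondary outcomes). The second scan is made only if adjustment is needed ({11a}). With no adjustment, the volume is 0. Nothing in the definition separates a splint left alone because it fits from one left alone because it is loose.

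**Step 2. Who sets the score.** The treating dentist adjusts, and the treating dentist is not blinded ({16b}, {17a}). The documents give nothing from which to size this bias.

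**Step 3. Simple illustration.** Assume a share p of printed splints is loose and left alone, and the rest need the same mean adjustment M as milled splints.

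- Printed mean = (1 − p) × M + p × 0 = (1 − p) × M.
- With 10 of 40 printed splints loose (assumed), p = 10/40 = 0.25 and the printed mean is 0.75 × M, a score 25% lower (apparently better).

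**Step 4. Illustration with a continuous fit offset.** Assume a signed offset X, normal with mean m and SD 1, positive when tight and negative when loose. Let adjustment = max(X, 0) and true misfit = |X|. With φ and Φ the standard normal density and distribution function:

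- Mean adjustment = mΦ(m) + φ(m)
- Mean misfit = 2φ(m) + m(2Φ(m) − 1)

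Milled splints are centred at m = 0. A simulation with one million draws per setting gave the same values to two decimals.

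| Printed mean offset (SD) | Mean adjustment, printed (milled 0.40) | Mean misfit, printed (milled 0.80) |
|---|---|---|
| 0 | 0.40 | 0.80 |
| −0.5 | 0.20 | 0.90 |
| −1 | 0.08 | 1.17 |
| −2 | 0.01 | 2.02 |

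Example at m = −0.5: adjustment = −0.5 × 0.309 + 0.352 = 0.198; misfit = 2 × 0.352 + (−0.5)(2 × 0.309 − 1) = 0.704 + 0.191 = 0.895.

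With no systematic shift, the two measures agree. With a shift towards looseness, the adjustment score improves while misfit worsens, and more participants would not cure this. With a shift towards tightness the ranking is right: at m = +0.5 mean adjustment is 0.198 + 0.5 = 0.698, above the milled 0.40, and mean misfit is again 0.90. The weakness lies on the loose side only.

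**Step 5. What else in the plan sees looseness.** The participants' stability rating does. It is blinded and compared by method, but it is subjective, is collected from 2 weeks onwards (after any adjustment at delivery), and does not enter the fit score.

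**The case against.** **The trial already measures looseness.** This is the strongest point, and it stands. Blinded participants rate stability for each splint twice, the ratings are compared by manufacturing method, and the item sits under the primary outcomes, above fit. A reader might infer from the fit definition that a loose process would go unnoticed; the documents do not support that. What remains is that the fit result and the stability result could disagree, and the article does not say how to read them together.

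**Adjustment is a legitimate clinical endpoint.** This also stands. The work needed at delivery matters to dentist and patient. The objection is to calling it fit.

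**Much of the mechanism has to be inferred.** A reader might assume that material is only ground away, or that inner and biting surfaces are pooled into one volume. The article says adjustment and does not state which surfaces are overlaid, whether the volume is signed, or how a loose splint is handled. These are details an article may leave to the full protocol, so neither reading is relied on here.

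**Jaw registration error could be thought to contaminate the comparison.** Both splints of a participant come from one registration and one design, and order is randomised, so this error should largely cancel within the person. It is not part of the point.

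**A wrong ranking has not been shown.** Correct. It needs systematic looseness in one process and no corrective adjustment, and neither is documented.

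**Conclusion.** The point holds in a limited form. As defined, the fit score is adjustment volume and nothing else, depends on the discretion of a dentist who knows the manufacturing method, and gives the best value to any splint left unadjusted. It can therefore favour a process that errs on the loose side.

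Its size is unknown. The 25% figure and the table rest wholly on assumed values and on the assumption that looseness triggers no volume change. They show that the direction can be wrong, not that it will be.

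The reach is narrow. Fit is one component of a secondary technical outcome and is not among the secondary outcomes named for the non-inferiority rule in Statistical methods {20a}. The primary OHIP-G14 analysis and the sample size are unaffected. A reader might take the point as a threat to the trial's main conclusion; the documents do not support that.

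**What to change.** In Secondary outcomes:

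1. Rename the measure as adjustment required at incorporation, and state that no conclusion on fit is drawn from it alone.
2. State that it is interpreted together with the participants' stability rating, by manufacturing method.
3. Where the as-delivered scans cover the inner surface, add the signed and the absolute deviation of the as-delivered scan from the common design file, per splint, as a supplementary measure of manufacturing accuracy. The inputs exist: both splints share one design ({6b}), the protocol already requires a "scan of the splint as delivered from the laboratory with the intraoral scanner", and overlay software with trained users is in place (Plans for assessment and collection of outcomes {18a}). These scans precede any adjustment, so the measure does not depend on the unblinded dentist. Sign separates loose from tight, and errors in the impression or design are common to both splints and largely cancel within a participant.

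Cost: 40 participants × 2 splints = about 80 extra overlays and a wording change, with no new visit, scan or participant. Two limits should be stated. The article does not say whether the delivery scan captures the inner surface, so this must be confirmed first. And deviation from the design measures manufacturing accuracy, not fit in the mouth, so it supplements the adjustment volume and the stability rating and does not replace them.

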## Data collection and management

### Plans for assessment and collection of outcomes {18a}

Data of the TMD cohort is collected and assessed by one trained and calibrated examiner according to the DC/TMD protocol. This examiner also trained the examiner collecting and assessing data of the bruxism cohort. Data will be collected via established diagnosis tools and patient questionnaires (BSI, DC/TMD symptom questionnaire, DC/TMD examination form, GCPS, OHIP-G14). These forms can be found on the following webpages:BSI can be downloaded from the webpage of the DGFDT (https://www.dgfdt.de/richtlinien_formulare)DC/TMD symptom questionnaire, DC/TMD examination form and GCPS (version 2.0) can be found in different languages on the webpage of the International Network for Orofacial Pain and Related Disorder Methodology (INfORM—https://ubwp.buffalo.edu/rdc-tmdinternational/tmd-assessmentdiagnosis/dc-tmd-translations/). Specifications on how to assess and diagnose a patient in a standardized way can also be found on this webpage. This trial applied the German forms.OHIP-G14 can be accessed in German via the Institute of German Dentists (IDZ- https://www.idz.institute/fileadmin/Content/Publikationen-PDF/IDZ-2005-Fragebogen_OHIP-G-14.pdf).

The completed questionnaires are then assessed as specified by the DGFDT and INfORM. All forms are standard forms and are commonly applied in the context of bruxism and TMD. Validity and reliability of the DC/TMD are well characterized. A myalgia, myofascial pain, and arthralgia can be diagnosed with a sensitivity of ≥ 0.86 and a specificity of ≥ 0.98 and with an inter-examiner reliability for the clinical assessment of kappa ≥ 0.85 [30]. The GCPS is recognized as a sensitive tool to detect minor changes in TMD symptoms [20] and OHIP-G14 shows a correlation with self-perception of oral health and physical and mental dimensions and shows satisfactory validity and reliability [31, 32].

Furthermore, the volume change of splints and opposing dentition is calculated by overlaying optical scans with the software Geomagic Control X (3D Systems, Moerfelden-Walldorf, Germany) by trained users of the software.

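### Splint wear, measured from incorporation to 3 months, includes any material removed when the splint is adjusted at the 2-week visit

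*Protocol article*

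**What the plan says.** Under Secondary outcomes, splint wear is the loss of volume found "by overlaying scans of the splints obtained at incorporation and the 3 months control". No other scan enters the definition. The same section has one outcome that measures adjustment, and it is limited to the day of insertion: "Fit at incorporation is evaluated by calculating the amount of adjustment necessary in µm^3^ by overlaying scans before and after adjustment of the splint".

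The visit protocol under Intervention description {11a} provides for scans at incorporation: "scan of the splint as delivered from the laboratory with the intraoral scanner and—if necessary—also after adjustment". At the 2-week control of the first splint (T2) it provides for "if necessary, adjustment and scan of the splint". The 2-week control of the second splint (T4) refers back to T2.

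Plans for assessment and collection of outcomes {18a} adds only that "the volume change of splints and opposing dentition is calculated by overlaying optical scans with the software Geomagic Control X". Statistical methods {20a} lists volume loss of the splint among the secondary outcomes tested for non-inferiority. Who will be blinded {17a} states that the treating dentists are not blinded, because trained staff can tell the two splint types apart.

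**The concern.** The 2-week visit lies between the two scans that define wear. If a dentist removes material at that visit, the 3-month scan shows the loss and the overlay cannot tell it from wear in use. The volume is not recorded elsewhere either, because the fit outcome stops at incorporation.

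At stake is the wear comparison, one of the technical results on which printed splints are to be judged. More 2-week adjustment of printed splints would make them appear to wear faster. More adjustment of milled splints would hide faster wear of printed ones. The crossover does not remove this, because adjustment belongs to the individual splint and not to the participant.

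**Working it through.** The plan states no figure for wear, for adjusted volume or for the share of splints adjusted, so there is nothing to reproduce. The check sets the definition against the schedule, then shows how the error behaves on assumed values.

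**Step 1: what the rule measures.** For one splint, let W1 be wear from incorporation to the 2-week visit, G the volume removed at that visit (zero if not adjusted), and W2 wear from then to 3 months. True wear is W = W1 + W2. The stated rule gives W1 + G + W2 = W + G.

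**Step 2: is G a volume of the same kind?** The documents speak of adjustment, not of grinding. But Secondary outcomes measures adjustment at incorporation in µm³ by overlaying scans, which is the unit and method used for wear. On the protocol's own terms the two quantities add.

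**Step 3: is G removed anywhere?** Secondary outcomes, {18a} and {20a} neither reset the baseline after an adjustment nor subtract its volume, and no listed outcome uses the 2-week scan.

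**Step 4: effect on the comparison.** Let q be the share of splints of one type adjusted at 2 weeks. Mean apparent wear is W + qG. With equal true wear and equal G in both types, the false difference is (q_a − q_b) × G. All values below are assumptions, in multiples of true wear W:

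| Share adjusted, type a / type b | G = 0.5 W | G = 1 W | G = 2 W |
|---|---|---|---|
| 20% / 20% | 0 | 0 | 0 |
| 40% / 20% | 0.1 W | 0.2 W | 0.4 W |
| 50% / 10% | 0.2 W | 0.4 W | 0.8 W |

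Example: (0.40 − 0.20) × 2 W = 0.4 W. Smaller G shrinks every entry in proportion.

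**Step 5: equal adjustment.** With 20% adjusted in both types, apparent wear is 1 + 0.2 × 0.5 = 1.1 to 1.0 + 0.2 × 2 = 1.4 times true wear in each. The mean difference is unbiased. The added term still varies between splints: for constant G its SD is G × √(q(1 − q)) = G × √(0.2 × 0.8) = 0.4 G, that is 0.2 W to 0.8 W over the same range. This adds to the variance if adjustment is unrelated to true wear.

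**Step 6: which incorporation scan?** At incorporation there may be two scans, before and after adjustment. The wear definition does not say which is the reference. If it is the earlier one, the incorporation adjustment is counted as wear as well as under fit.

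**The case against.** The strongest reply is that one sentence in a journal article should not be read as excluding the 2-week scan. That scan is planned, the article gives it no other purpose, and the full protocol, which is not shown, may use it as a new baseline. This does not carry the point: the article names the two scans that define wear, and nothing in it gives the 2-week scan that role. The reply does show that the problem lies more in the definition than in data collection, since a scan is already planned when a splint is adjusted.

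Three further objections stand.

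- **Direction and certainty.** A reader might infer that the wear comparison will be wrong. The documents do not support this. Both splints come from the same digital design (Explanation for the choice of comparators {6b}), each participant wears both, and nothing shows that 2-week adjustment differs by type.
- **Size.** A reader might also infer that the error rivals or exceeds wear itself. That follows only from choosing an adjustment volume as large as the wear. No such figure is in the documents.
- **Remedy.** Simply starting the clock at 2 weeks for adjusted splints drops their early wear while unadjusted splints keep theirs. Dividing by weeks worn repairs this only if wear is linear in time, which nothing in the documents supports.

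**Conclusion.** The point holds on the wording: for any splint adjusted at T2 or T4, the stated rule reports wear plus adjustment. For those splints wear is overstated, and the variance of the outcome rises. Bias between printed and milled splints is conditional on adjustment differing by type in frequency or amount. The unblinded dentists make a difference possible; they do not show that there is one. The size is unknown, and the table only illustrates the mechanism.

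The conclusion rests on adjustment meaning removal of material, which the protocol's own volumetric measure of adjustment supports. It affects one secondary outcome and only splints adjusted at 2 weeks. The OHIP-G14 analysis and the sample size are untouched. It should be corrected, because the correction is cheap.

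**What to change.** Define splint wear as the sum of volume losses over intervals without adjustment:

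- Splints not adjusted at T2/T4: from the post-adjustment incorporation scan (the only scan, if no adjustment was made then) to the 3-month scan.
- Splints adjusted at T2/T4: from that same incorporation scan to a scan just before the 2-week adjustment, plus from a scan just after it to the 3-month scan.

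Report the T2/T4 adjustment volume by splint type as a separate item, leaving fit at incorporation as defined. State that the 2-week scan already planned is taken after adjustment; the present wording does not fix the order.

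The cost is a change of wording and one extra splint scan before adjustment, for adjusted splints only. With 40 participants and two splints each, that is at most 80 scans. No clinical rule changes.

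Where the pre-adjustment scan is not available, for instance because visits have already taken place, use the post-adjustment T2/T4 scan as baseline for adjusted splints and state that their first two weeks are excluded. With the 3-month control at 11 to 13 weeks, this omits 2/13 to 2/11 of the period, about 15% to 18%. Report the incorporation-to-3-months definition as a sensitivity analysis. For an adjusted splint the two results are W2 and W1 + G + W2, so, measurement error aside, true wear lies between them. The difference between splint types need not lie between the two corresponding estimates.
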